### Efficacy analyses

Our primary endpoint and first analysis of data will be the end of the 12-week RCT. Analysis will involve a summary of within- and between-group comparisons with respect to the primary and secondary outcome measures detailed above using paired *t*-test/McNemar’s test, *t*-test, and analysis of variance (ANOVA)/Kruskal-Wallis test analyses, as appropriate. In addition, (the simple and/or multiple) linear regression/general linear model/generalized linear model approaches will be performed, adjusting for the factors employed in minimizing participants to groups, as appropriate.

The second endpoint and planned analysis will be at the 24-week stage to examine the effect of 12 weeks’ intervention across all 100 participants. The final analysis of long-term effects will examine all 100 participants at trial completion (36 weeks).

Subgroup analyses will be performed to identify a participant population that demonstrates the most clinically significant improvement.

EEG recordings (only performed on half of the participants) will be analyzed using EEGLAB [29], an open source toolbox for advanced EEG analysis (Swartz Center for Computational Neuroscience (SCCN), University of California San Diego, CA, USA) run under MATLAB (The Mathworks, Natick, MA, USA). Pre-processed data (high- and low-pass filtering, offline epoching, artifact correction) will be further corrected for artifacts using independent component analysis (ICA) in EEGLAB [30]. Power analysis will be carried out in the EEGLAB, and obtained power spectra will be divided to analyze oscillatory activity in normalized EEG frequency bands. Analysis of sources of spontaneous oscillatory activity will also be conducted in EEGLAB (and/or standardized low resolution brain electromagnetic tomography (sLORETA)). Non-parametric statistical tests will be used to test for significant differences in any change in oscillatory activity between the placebo and intervention group. Within-group comparisons of activity recorded pre- and post-intervention will also be performed.

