### Population and sample size

Participants will be recruited through leaflets placed in audiology, and ear, nose and throat (ENT) departments, and any direct contacts made to the recruiting centers in response to publicity in the national media. Written informed consent will be obtained from each participant in accordance with the permissions granted. The primary outcome measure of treatment efficacy is the Tinnitus Handicap Questionnaire (THQ) [17], where the maximum score is 2,700. THQ data from a published study of tinnitus maskers were used to estimate the required sample size (two-sample *t*-test power analysis, performed in *R*). After a 12-week intervention, Henry *et al*. [18] found that a difference in mean THQ score of 194 between groups with a pooled standard deviation (SD) of 450 was considered significant, and represented a medium effect size. If we therefore assume a difference in mean THQ score of 250 between groups with a pooled SD of 425 as representative of a large effect size, then for a two-sided significance level of 0.05 and 80% power, it is estimated that 47 participants are required for each group. We assume a low drop-out rate of approximately 5% in 12 weeks and therefore a total of 100 participants will be recruited.

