### Randomization and blinding

Randomized allocation to groups will be based on a minimization protocol (Minim) [21] and conducted by a researcher who is independent of the trial. Minimization will be used here to match groups for age: 18 to 49 years, 50 to 69 years, 70 or over years (categories based on statistics for moderate to severe hearing loss sourced from the Royal National Institute for Deaf People, now Action on Hearing Loss [22]), gender, hearing loss (PTA at 0.5, 1, 2, 4 kHz), and grade of tinnitus severity (using THI categories defined in [23]).

Participants will be randomly assigned initially to receive the treatment (Group 1) or placebo (Group 2) stimulation. After 12 weeks, participants in the placebo group will crossover to start receiving the treatment according to the intervention algorithm, and will follow the same protocol as initially delivered to Group 1.

The RCT phase of this study will be conducted double-blind. Participants will not know the group to which they are allocated (intervention or placebo). The researcher assessing outcomes will not know which group the participant was allocated to. The audiologists fitting and adjusting the device will be blind to group allocation since they will be unaware whether the device programming code supplied to them after the participant is randomized generates an intervention or placebo stimulus. All participants will receive the same information about the expected trial outcomes.

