### Primary outcome measure

The primary measure of efficacy will be change in THQ score between baseline and week 12. At the time of writing the protocol for the funding application, this questionnaire was one of the better validated measures of tinnitus severity, responsive to treatment-related change, and with a test-retest reliability of 0.93 [24]. The sample size is powered according to previous trial data using this measure [18].

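### Baseline THQ is missing from the stated adjustment set although the primary outcome is change in THQ; adding it costs almost nothing, and the plan should say whether the SD of 425 is of scores or of change

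*Protocol article*

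**What the plan says.** All references are to the Protocol article.

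- **Primary outcome measure:** "The primary measure of efficacy will be change in THQ score between baseline and week 12". The same section quotes a test-retest reliability of 0.93 for the THQ and says the trial was powered from earlier data on this questionnaire.
- **Population and sample size:** a two-sample t-test calculation that assumes "a difference in mean THQ score of 250 between groups with a pooled SD of 425", "for a two-sided significance level of 0.05 and 80% power", from which "it is estimated that 47 participants are required for each group". The precedent is a masker study in which "a difference in mean THQ score of 194 between groups with a pooled standard deviation (SD) of 450 was considered significant". No SD of change and no correlation between baseline and week 12 is given. With about 5% drop-out the total is 100.
- **Randomization and blinding:** the minimisation factors are age band, gender, hearing loss (PTA) and THI severity grade. THQ is not among them.
- **Efficacy analyses:** paired t-test/McNemar, t-test and ANOVA/Kruskal-Wallis, and additionally linear or generalised linear models "adjusting for the factors employed in minimizing participants to groups, as appropriate". No test is named as the primary one.

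**The concern.** Baseline THQ is likely to be the strongest available predictor of week-12 THQ. The plan uses it only through subtraction. Subtraction gives baseline a fixed coefficient of 1, whereas the best coefficient, with equal SDs at the two visits, is r. When r is below 1, subtraction over-corrects. Precision is lost, and an arm that starts higher by chance tends to show a larger fall through regression to the mean.

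Reading ANOVA as a repeated-measures group-by-time test does not change this. With two time points that test is the change-score t-test.

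A second matter is tied to the first. The sample size is worded as a difference in THQ scores, while the endpoint is change. Whether the stated 80% carries over to an unadjusted test of change depends on what the SD of 425 measures, and the text does not say.

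**Working it through.** **Inputs.** Difference 250, SD 425, two-sided 0.05, 47 per arm, precedent 194 with SD 450 (Population and sample size); reliability 0.93 (Primary outcome measure). The correlation r is not given, so it is an assumption and a range is shown.

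**1. Reproduce the plan's figure.** d = 250/425 = 0.588. Two-sample t-test, noncentral t: 46 per arm gives 79.7% and 47 gives 80.6%, so 47 reproduces. Drop-out: 94/0.95 = 98.9, or 99, against 100 planned.

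**2. Relative precision.** With equal SDs at both visits, the variance of change is 2(1 − r)SD² and the baseline-adjusted residual variance is (1 − r²)SD². Their ratio is 2(1 − r)/[(1 − r)(1 + r)] = 2/(1 + r), and SD cancels:

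- r = 0.5: 2/1.5 = 1.33
- r = 0.7: 2/1.7 = 1.18
- r = 0.93: 2/1.93 = 1.04

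**3. Power, if 425 is the SD of scores at one time point, equal at both visits** (47 per arm, difference 250). SD of change = 425√(2(1 − r)); adjusted SD = 425√(1 − r²).

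| r | SD of change | Power, change score | Adjusted SD | Power, adjusted |
|---|---|---|---|---|
| 0 | 601.0 | 51.4% | 425.0 | 80.6% |
| 0.3 | 502.9 | 66.5% | 405.4 | 84.1% |
| 0.4 | 465.6 | 73.1% | 389.5 | 86.8% |
| 0.5 | 425.0 | 80.6% | 368.1 | 90.3% |
| 0.6 | 380.1 | 88.4% | 340.0 | 94.1% |
| 0.7 | 329.2 | 95.4% | 303.5 | 97.7% |
| 0.8 | 268.8 | 99.4% | 255.0 | 99.7% |
| 0.93 | 159.0 | about 100% | 156.2 | about 100% |

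Solving for 80% power of the change-score test gives r = 0.493 with 47 per arm and r = 0.460 with 50 per arm.

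**4. The same at the precedent effect** (194, SD 450, 47 per arm), change score against adjusted: r = 0.5, 54.3% and 66.6%; r = 0.7, 76.1% and 82.5%; r = 0.8, 90.5% and 93.1%.

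**5. Cost in degrees of freedom.** Spending seven more degrees of freedom on covariates (92 down to 85) moves the adjusted power at r = 0.5 from 90.3% to 90.2%.

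**6. Chance imbalance, on the same reading of 425.** The standard error of the baseline difference is 425√(2/47) = 87.7 points. Given a baseline difference D, the change-score estimate is shifted by (1 − r)D in size. For D of one standard error this is 0.5 × 87.7 = 43.8 points at r = 0.5, 0.3 × 87.7 = 26.3 at r = 0.7, and 0.07 × 87.7 = 6.1 at r = 0.93, against a target of 250. Balancing on THI grade should make such imbalances somewhat smaller.

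**The case against.** **The change-score comparison is valid.** This stands. It uses each participant's own baseline and is unbiased over randomisations. The point is about efficiency and conditional imbalance.

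**THI grade already covers baseline severity.** In part. It is balanced by minimisation and is in the adjustment set. But it is a coarse category of a different questionnaire, entry is limited to THI 18 to 77, and THQ can still vary within a grade.

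**The quoted reliability of 0.93 makes r high, so little is lost.** This has weight. Near 0.93 the gain is about 4% in variance, and nothing in the document suggests r below 0.5. But a 12-week correlation under treatment should be lower than test-retest reliability, so 0.93 is an upper guide. The adjusted analysis is ahead at every r below 1.

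**The covariate list belongs in the full analysis plan.** A fuller plan may add baseline THQ. Yet the article does not leave the set open: it names one, and the baseline of the primary outcome is not in it.

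**Stronger readings that the text does not support.** A reader might infer that 80% power for change requires r of at least 0.5. That follows only if 425 is a single-visit SD, equal at both visits; if it is an SD of change, the condition disappears. A reader might also infer that the unadjusted t-test is the designated lead analysis. The Efficacy analyses section gives a menu and ranks nothing.

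**Conclusion.** The point holds as a free gain in precision and in protection against baseline imbalance. Without baseline THQ in the model, the change-score comparison carries 33% more variance at r = 0.5, 18% more at r = 0.7 and about 4% more at r = 0.93. These ratios assume equal SDs at both visits and a linear relation; they do not depend on the value of the SD.

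The power statement is conditional. If 425 is the SD of scores at one visit, an unadjusted test of change reaches 80% only when r is about 0.49 or more with 47 per arm (0.46 with 50), while the adjusted analysis stays at about 80% or above for any r. The document does not settle what 425 is and gives no r.

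It would be wrong to conclude that the trial is underpowered. The stated sample size reproduces, and the one within-person figure given points to a fairly high correlation.

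**What to change.** - Name one primary analysis: a linear model of week-12 THQ (or change, which gives the same treatment effect once baseline is in the model) on treatment, continuous baseline THQ and the four minimisation factors. Report the adjusted difference with its 95% CI.
- Make the unadjusted t-test and the within-group tests supportive.
- Analyse THI, TFI and WHOQOL-BREF the same way, each with its own baseline.
- In Population and sample size, state whether 425 is an SD of scores or of change. If it is of scores, give the correlation assumed, or say that the power refers to the baseline-adjusted analysis.

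This is a change of wording plus a few degrees of freedom. No new data are needed, and the article reports that recruitment is still under way, so the change can be made before any unblinded analysis.

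### The stated subgroup aim is to find the population that improves most, which will name a responder group even if the device has no effect

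*Protocol article*

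**What the plan says.** The subgroup plan is one sentence in the Efficacy analyses section: "Subgroup analyses will be performed to identify a participant population that demonstrates the most clinically significant improvement". It follows the descriptions of the 12-, 24- and 36-week analyses. It does not say whether improvement is change within a group or the difference between arms. The same section plans both kinds of comparison.

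The outcome and scale come from two other sections. Primary outcome measure states: "The primary measure of efficacy will be change in THQ score between baseline and week 12". Population and sample size takes as its design values "assume a difference in mean THQ score of 250 between groups with a pooled SD of 425 as representative of a large effect size". As background it reports that a published masker study "found that a difference in mean THQ score of 194 between groups with a pooled standard deviation (SD) of 450 was considered significant".

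The only factors with a fixed role in the design are the four minimisation factors under Randomization and blinding: age in three bands, gender, hearing loss and THI severity grade. No number of levels is given for the last two. The statistical methods section also lists about ten baseline variables to be described, and leaves that list open.

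**The concern.** Looking for the subgroup that did best is a selection rule. Its answer is the maximum of a set of estimates, and a maximum is biased upward whenever the estimates carry error. One subgroup must rank first, so the exercise cannot return the answer that there is no responder population.

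The criterion is also not tied to the control arm. After week 12 the placebo group crosses over, so at weeks 24 and 36 no concurrent placebo comparison remains. A search on change alone would credit the device with anything that moves scores in both arms.

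At stake is a responder claim from a trial of 100 people that presents itself as high-level evidence, for a device that the article says is already in clinical use. The primary 12-week comparison is not affected.

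**Working it through.** **1. Reproduce the plan's figure.** Inputs from Population and sample size: difference 250, SD 425, two-sided 0.05, power 80%. The normal approximation gives n = 2 × (1.960 + 0.842)² × 425² / 250² = 45.4, so 46 per group. The two-sample t-test gives 46.35, so 47, as stated. With 5% drop-out, 94 / 0.95 = 98.9, consistent with recruiting 100.

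**2. Precision inside a subgroup.** The standard error of a between-arm difference with n per arm is 425 × √(2/n).
- Whole trial, n = 47: 87.7 points. The smallest observed difference reaching two-sided p<0.05 is 174 points.
- Half of each arm, n = 23.5: 124 points.
- A third of each arm, n = 15.7: 152 points.
- A fifth of each arm, n = 9.4: 196 points.

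**3. Closed-form check.** For k disjoint equal subgroups with no effect, the expected largest difference is E[max of k standard normals] × 425 × √(2/n). Gender alone (k = 2): 0.564 × 124 = 70. Age alone in thirds (k = 3): 0.85 × 152 = 129.

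**4. Simulation with no device effect.** Assumptions: normal outcome, SD 425, 47 per arm, factors independent of one another, at least 5 per arm in each level, 3,000 to 6,000 runs. In each run the largest difference favouring the device was kept. The number and frequency of levels are assumed, apart from the three age bands and two genders.

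| Set searched | Levels | Mean best difference | ≥194 | ≥250 | Any level nominally significant for the device |
|---|---|---|---|---|---|
| Gender | 2 | 72 | 11.9% | 4.2% | 4.8% |
| Two binary factors | 4 | 102 | 18.3% | 7.9% | 8.6% |
| Age and gender | 5 | 140 | 30.4% | 16.2% | not run |
| Four binary factors | 8 | 131 | 26.5% | 11.8% | 13.1% |
| Four minimisation factors, even levels | 10 | 183 | 45.0% | 26.4% | 16.5% |
| Same, uneven levels | 10 | 204 | 50.7% | 33.0% | 16.4% |
| Ten binary factors | 20 | 172 | 41.3% | 21.7% | 23.1% |
| Ten three-level factors | 30 | 268 | 75.1% | 55.6% | 35.7% |

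Variants of the four-factor case:
- Levels exactly balanced between arms: 178 (even), 199 (uneven), 193 (hearing in three levels).
- 50 per arm, even levels: 179, with 17.2% nominally significant for the device.
- Uneven levels with at least 10 per arm required: 153.

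**5. Comparison with the article's figures.** The four-factor range of 178 to 204 is 71% to 82% of the assumed 250 (178/250, 204/250). It is 92% to 105% of the 194 reported for the masker study (178/194, 204/194).

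**6. Dependence on the SD.** The article gives no SD for change. If 425 is the SD of a single score and the baseline to week 12 correlation is ρ, the change-score SD is 425 × √(2(1−ρ)). That is 425 at ρ = 0.5 and 329 at ρ = 0.7, both assumptions. The point figures scale in proportion: 178 × 329/425 = 138 and 204 × 329/425 = 158. The 17% does not depend on the SD.

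**7. Error rate for one direction.** A single two-sided 0.05 test favours the device by chance 2.5% of the time. Ten independent tests would give 1 − 0.975¹⁰ = 22.4%. The levels share participants, which brings the rate down to about 17%.

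**The case against.** The strongest reply is that this is a condensed article. Subgroup lists, interaction tests, multiplicity rules and exploratory labels normally sit in the analysis plan, and nothing here calls the subgroup work confirmatory. That stands as far as it goes, and the absence of those details is not the point. The point is the aim that the article does state: an analysis plan faithful to it would still pick a maximum.

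Second, the size depends on subgroups the article never names. This is correct. The minimisation factors are listed for allocation, not for subgrouping, and the result runs from about 70 to 270 points at SD 425. No single figure can be attached to the sentence without stating the set searched.

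The article does not support several stronger readings that a reader might infer:
- *Chance alone reproduces the effect that this trial calls significant.* The 194 (SD 450) belongs to the cited masker study. The trial assumes 250, and the four-factor result falls short of it.
- *About a third of null trials would yield a false responder group.* Roughly 32% to 35% show some subgroup at two-sided p<0.05, but that counts subgroups in which the device looks worse. In the device's favour it is about 17%.
- *Regression to the mean would push high-baseline subgroups to the top.* This is plausible if change alone is ranked, but the simulation has no baseline values and does not measure it.
- *The benefit is a clinically significant one.* The only such threshold in the article is 13 TFI points, which a THQ mean difference does not model.

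**Conclusion.** The concern holds for the rule as written. It selects the best of several noisy estimates, does not tie improvement to placebo, and will name a population whether or not the device works.

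If the levels of the four minimisation factors are searched, a null device would be expected to show a best-subgroup benefit of about 180 to 200 THQ points, and about 140 to 160 if the change-score SD is 329. The chance of a nominally significant subgroup favouring the device is about 17% instead of 2.5%. These figures rest on about 10 levels with assumed frequencies, 47 to 50 per arm, at least 5 per arm in each level and, for the 180 to 200, SD 425 applied to change. The direction of the bias needs none of these assumptions. The 12-week primary comparison and the sample size are untouched.

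**What to change.** Replace the subgroup sentence with:

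> Subgroup analyses are exploratory. Treatment-by-factor interactions for the four minimisation factors (age, gender, hearing loss, THI grade) will be tested on 12-week THQ change in a linear model adjusted for baseline THQ and the minimisation factors. All subgroups will be reported as between-arm differences with 95% CIs and interaction p-values, and no subgroup will be claimed as a responder population on the basis of having the largest improvement.

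This needs no new data, no change in sample size and no method outside those the section already lists. It also keeps the comparison at week 12, while a concurrent placebo arm exists.

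The cost is that the trial gives up a headline responder claim that it could not support. The interaction tests will also have little power. For a factor that splits each arm in half, the standard error of the interaction is √(124² + 124²) = 175 points, twice that of the main comparison. A non-significant interaction should therefore not be read as evidence that the effect is uniform.

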### Safety analysis

Adverse events that occur during the trial will be recorded and reported according to the trial sponsor’s standard operating procedure (SOP) for medical device trials (Nottingham University Hospitals NHS Trust SOP 52).

## Discussion

Various forms of sound and sound enrichment are in use for the clinical management of tinnitus. Typically sound is used to either mask tinnitus (introduce enough sound energy to cover up the percept of tinnitus and provide a temporary relief), partially mask tinnitus (reduce the percept so that the patient can adjust or ‘habituate’ to the sound), or to promote relaxation or distract attention away from the tinnitus sound [31]. Such approaches clearly target the psychological component of tinnitus (the negative emotional reaction), but are not clearly linked to any putative physiological mechanism of tinnitus generation. Acoustic CR® neuromodulation, however, explicitly targets a physiological marker of tinnitus, that of pathological synchronous oscillatory activity in the brain [32-35], measurable using EEG.

To generate high-level evidence for the efficacy of CR® neuromodulation, the RCT described here was designed to meet the reporting standards defined in the Consolidated Standards of Reporting Trials (CONSORT) Statement [36]. The RCT design also addresses the recent call for an international standard within the tinnitus community [37] in the form of a powered, blinded RCT with a mix of meaningful and validated outcome measures, to best capture clinical significance and change in tinnitus percept and related physiology.

## Trial status

The trial is currently in recruitment phase.

## Abbreviations

ANOVA: Analysis of variance; BAI: Beck anxiety inventory; BDI-II: Beck depression inventory; CONSORT: Consolidated standards of reporting trials; CR: Coordinated reset; EEG: Electroencephalography; ENT: Ear, nose and throat; ICA: Independent component analysis; LTE: Long-term extension; NHS: National Health Service; NIHR: National Institute for Health Research; NRES: National Research Ethics Service; PTA: Pure-tone average; RCT: Randomized controlled trial; SCCN: Swartz Center for Computational Neuroscience; SD: Standard deviation; sLORETA: Standardized low resolution brain electromagnetic tomography; SOP: Standard operating procedure; TFI: Tinnitus functional index; THI: Tinnitus handicap inventory; THQ: Tinnitus handicap questionnaire; UCL: University College London; WHO: World Health Organization; WHOQOL-BREF: WHO quality of Life-BREF.
